## Abstract

**Introduction:**

Diabetes self-management education (DSME) helps patients self-manage their condition and improve outcomes/quality of life. However, access to DSME is limited, particularly in low-income areas. This study aims to develop a DSME training kit (EK-DIN), understand barriers to implementation, and evaluate the effectiveness and sustainability of community leader (CL)-based rollout using a stepped wedge cluster randomized trial format.

**Methods and analysis:**

The mixed methods study will begin with a qualitative study to evaluate the facilitators and barriers towards CL-based DSME. The in-depth interview notes will be transcribed for thematic analysis. These results will be utilized for a stakeholder’s workshop to develop the EK-DIN kit, a patient-interfacing app, and an implementation plan. Rollout will be conducted in 30 clusters in Delhi, preselected by the DEDICOM-II survey in 5 steps (6 clusters every 3 months: 2 each from each socio-economic category; randomly selected per sequence). A CL from each cluster will be trained in using the EK-DIN kit/app over 1 month. The trained CL will conduct DSME sessions among the cluster residents using the EK-DIN kits provided fortnightly for 3 months. Compliance and blood parameters data will be collected at baseline, 3 months after the intervention, and every quarter thereafter till completion. Change in HbA1c before and after the intervention will be evaluated as the primary outcome using the swCRTdesign package for R version 4.0.2 and the swSummary function. The sustainability of the effects will be evaluated using the change in quarterly parameters after intervention completion.

**Discussion:**

A positive result will set the template for a generalizable public health intervention with proven community effectiveness, sustainability, cost-effectiveness, and positive quality-of-life impact. While a negative result will require the testing of alternative approaches, it would still add substantially to existing knowledge on the subject. Given the diverse socio-cultural setting in which the trial is being proposed and the high power of the study, the results (positive or negative) should be widely applicable and have policy implications.

**Trial registration:**

CTRI/2023/07/054963. Date of Registration: 7th July 2023.

## Administrative information

The numbers in curly brackets in this protocol refer to SPIRIT checklist item numbers. The order of the items has been modified to group similar items (see http://www.equator-network.org/reporting-guidelines/spirit-2013-statement-defining-standard-protocol-items-for-clinical-trials/).

## Background

Type 2 diabetes is a major public health problem, with an estimated 537 million adults worldwide. In India alone, the numbers exceed 101 million and are expected to increase to 134 million by 2045 [1]. Despite its documented high and rising prevalence, serious long-term complications, and established evidence-based guidelines for management, the translation of practice recommendations to care is still deficient [1, 2]. This, in turn, contributes to a high risk of complications, cost, and mortality.

With this background, we undertook two community surveys on the Quality of Diabetes Care and associated cardiovascular risks in Delhi in 2005–2006 [3] and, more recently, in 2018–2020 [4] (DEDICOM and DEDICOM-II; funded by ICMR). Both house-to-house 30-cluster surveys showed that the quality of diabetes care delivered to diabetes patients in Delhi was consistently poor. Although not directly comparable due to differing population sets, it is noteworthy that the percentage of subjects with extremely poor diabetes control (HbA1c > 10) was significantly higher in the second survey compared to the first one. This implied a progressively deteriorating situation and emphasized the urgent need for an effective intervention plan to address the problem.

An important lacuna in the existing strategy [5] for diabetes management [6] is that it relies on setting up care services and puts the onus of delivery of quality care on the public health care delivery system. While the availability of good healthcare services is an important determinant of disease management [6], it has been amply demonstrated that diabetes lifestyle modification (LSM) and diabetes self-management education (DSME) are the two most critical determinants of success beyond drugs and tests [6]. Empowering the individual in a patient-centric manner improves awareness and helps with risk modification and care-seeking behavior in a manner complementary to good medical advice. However, attempts to deliver DSME and LSM at scale through the doctor/diabetes educator approach [7, 8] have met with limited success leading to the search for unconventional options. Several systematic reviews [9–11] have documented that group-based education is more effective than individual-based interventions in improving self-efficacy, glycemic control, lipid profile, blood pressure, body weight, and psychosocial outcomes. Several eminent international studies have also established the utility of community-based, peer-led prevention programs globally and showed improvement in glucose and metabolic control [6, 9, 12, 13]. Digital interventions alone have also been found to be effective globally [14]. However, there is wide variability in such results emanating from local contextual factors/skill levels of trainers. Hence, we hypothesize that a combined approach merging the peer-led and digital streams, and standardizing intervention delivery will maximize community effectiveness.

We are therefore proposing the current work to locally co-develop an educational kit for diabetes intervention (EK-DIN; meaning One-Day in Hindi). We will then evaluate its effectiveness in improving the quality of diabetes care when EK-DIN is used for diabetes self-management education by community leaders. The rollout and evaluation will be done as a stepped wedge cluster randomized trial conducted among the re-consenting participants of the DEDICOM-II survey.

## Study objectives

### Primary objective

To co-develop a culturally embedded and locally tailored novel self-management education module with known diabetes patients (EK-DIN kit and app) and to evaluate its effectiveness when implemented through a community-leader group-based format in improving the quality of diabetes care (biochemical parameters and preventive processes).

### Secondary objectives

To evaluate the effectiveness of DSME implemented using EK-DIN through a local community leader group teaching format in reducing cardiovascular risk among known diabetes patients.To compare the effectiveness of EK-DIN in improving the quality of diabetes care between socio-economic categories.To evaluate the cost-effectiveness of the EK-DIN kit when implemented through a community leader format.To assess the quality-of-life impact of a culturally embedded and locally developed novel self-management education module (EK-DIN).

## Methods

### Study design and setting

This study is proposed as a sequential mixed methods design. A summary of the study design is depicted in Fig. 1. As presented, the study comprises three phases—the first phase involves qualitative study to understand barriers and facilitators to intervention adoption among diabetes patients, the second phase involves intervention development by participative stakeholder engagement, and the third phase involves a subsequent intervention evaluation phase involving a stepped wedge cluster randomized trial (Sw-CRT) in Delhi among the participants of the DEDICOM-II survey, India.

**Fig. 1 Fig1:**
[figure not shown]
Summary of study design

### Procedure

#### Phase 1: Qualitative work

As a first step, we propose to conduct qualitative work among ~ 15 diabetes patients from each socio-economic category or till saturation is achieved. This will be used to evaluate the existing knowledge of the subjects about diabetes, their perception of how they could be helped to manage their condition better, and to document the potential facilitators and barriers for successful intervention. Gathering this information would enhance our understanding of the perceived need for the intervention and help us define more patient-centric outcomes. Incorporation of the patient perspective would also help to fine-tune the study design towards improving the sociocultural acceptability and improving compliance with the proposed intervention/follow-up. In this phase, in-depth interviews will be conducted on known diabetes patients with prior informed consent. The audio-recorded consent will be taken by the interviewer before starting the interview. Interviews will be audio-recorded for subsequent transcription. A semi-structured topic guide comprising several open-ended, semi-structured, pre-designed questions will be developed and piloted to direct interviews while remaining sensitive to unsolicited themes. Probes will be used where necessary. An interviewer with prior qualitative research training will conduct the interviews using an “inductive” approach in English or Hindi. Data will be collected in patients’ homes, assuring natural settings and maximizing patient comfort. Thematic analysis will be conducted, and this information will be used to guide phase 2.

#### Phase 2: Development of intervention (EK-DIN kit/app and implementation plan)

Building on the learnings from Step 1, a locally and culturally tailored intervention guided by the ADA guidelines [15] on lifestyle modification (LSM) and diabetes self-management education (DSME) will be developed. The intervention will have three components—an education-based kit for diabetes intervention (EK-DIN), an analogous app, and an implementation plan. A stakeholders panel will be constituted, including diabetologists, public health experts, diabetes educators, patient representatives, creative design experts, software engineers, and investigators. They will conduct focus group discussions towards designing the EK-DIN kit in English and Hindi for use by community leaders for delivering DSME and LSM. EK-DIN will include audio-visual aids and training materials, including the use of glucometers and self-monitoring BP instruments. Software experts will be briefed in the FGDs towards developing an app capable of hosting LSM and DSME audio-visual content, a self-tracking interface for self-review of blood sugars and other reports, and provision for timely reminders on due dates for investigations/consults in a bilingual patient-centric format. An implementation plan, including the preferred types of trainers, locations of the training, days of activities, and the language of training, will also be finalized in the focus group discussions.

#### Phase 3: Implementation of the intervention (stepped wedge cluster randomized trial (Sw-CRT))

The community intervention phase of the study will begin with a pilot on 10 known diabetes subjects from a nearby locality. The information gathered through the pilot will be used to further fine-tune the rollout plan. After the pilot, the rollout will target to recruit 350 diabetes patients from among the subjects of the DEDICOM-II survey [4]. It is expected that it will be possible to recruit ~ 12 subjects per cluster from among the 20–30 subjects/cluster recruited for the earlier survey [4]. All earlier clusters and participants will be eligible for recruitment in the proposed study and will be approached for informed consent.

The intervention will be rolled out using the stepped wedge cluster randomized trial format, as summarized in Figs. 2 and 3. As presented in this design, clusters enter the intervention arm sequentially, contributing control and intervention data, unlike traditional cluster-randomized clinical trials. The design involves 5 groups of clusters (6 clusters in each group; 2 each from lower, middle, and higher strata) with sequential cluster group crossover from control to intervention until all are exposed. Each cluster group will be pre-specified based on geographical contiguity. The order of rollout in the cluster groups will be determined by a computer-generated random sequence. The sequence will be concealed in opaque sealed envelopes till use. While blinding is not considered feasible at the participant/field staff level, the laboratory processing, data entry, statistical analysis, and investigators will be blinded to the sequence of intervention.

**Fig. 2 Fig2:**
[figure not shown]
Stepped wedge cluster randomized trial: SPIRIT flow diagram *Intervention and assessments explained in Fig. 3

**Fig. 3 Fig3:**
[figure not shown]
Trial rollout sequence

As presented in Fig. 3, at Step 0, each cluster group starts as a control condition, with the first cluster group initiating the preparation phase and contributing control data. In Step 1, cluster group 1 enters the intervention period. Three months later, another cluster group (6 clusters) enters the intervention period. This process continues until all clusters enter the intervention. Hence, the stepped-wedge trial design involves 3 months of data in pre-intervention and 18 months in post-intervention conditions for cluster group 1, followed by 6 months in pre-intervention and 15 months in post-intervention conditions in cluster group 2, and so on. All 30 clusters will be completed in 5 steps. The study design has been specifically chosen due to the documented inherent sample size, ethical, logistical, and naturalistic advantages of a wedge cluster rollout [16] and to evaluate the baseline status, impact of intervention, and sustainability of any benefits achieved.

For each cluster group, participants of the DEDICOM-II survey will be invited for recruitment by the research team in accordance with the following selection criteria.

### Eligibility

#### Inclusion criteria

Subjects recruited in our earlier survey of DEDICOM-IIKnown case of type 2 diabetes mellitus > 1 year (diagnosed by a registered medical practitioner using at least one blood glucose estimation)

#### Exclusion criteria

Subjects with cancer, renal, hepatic, or intestinal disease requiring continuing treatment or hospital admission (> 1 week in last 1 year)Subjects with inability to communicate (mental illness or physical disability)

A written informed consent form will be taken from all the participants prior to the recruitment by the research team. A baseline evaluation of eligible participants will be done, including the HbA1c, lipid profile, blood pressure, and compliance to the frequency of processes of care like eye examination, foot examination, and urine testing. A baseline evaluation of the quality of life using the QOLID tool [17] and cost of care will also be conducted. Quarterly evaluations for clinical assessment, blood investigations, and interval morbidity will continue in all groups. In the month preceding rollout in each cluster, a community leader (CL) will be identified.

### Community leader (CL)

CL will be from among the prominent interested diabetes patients involved in the local administration (RWA president or village head etc.; preference will be given to any person with any medical background like doctor, dietician, or nurse). The CL will be trained (training of trainers) in how to educate for LSM/DSME and improve your own care using EK-DIN over a 1-month period (education sessions of minimum 50 h). The value of the CL in delivering the intervention is expected to stem from their direct experience with the community and participants’ living situations. They will be capable of support and empathy which often is difficult for professionally trained individuals to provide. They will have a first-hand understanding of the myths, beliefs, and cultural remedies that may interfere with the adoption of health recommendations.

As the intervention in the cluster begins, the CL will then conduct 2-h DSME sessions among the particular cluster residents using the EK-DIN kits provided at a pre-specified site fortnightly for 3 months. The classes will be conducted on a public holiday, will be locally advertised, and will be open to all interested. Family members, friends, and/or caretakers will be encouraged to attend. The blood glucose monitoring logs of each participant will be reviewed at the beginning of each session. A mop-up round will be conducted for the subjects who missed the training. In case any participant is unable to attend the 2 rounds of training, video consult modalities will be utilized to administer the intervention. After training, each participant will be provided with self-tracking sheets in manual/electronic format as envisaged and developed in phase 2. Whenever the CL notes that the participants are not meeting the treatment goals, they will encourage the patients to follow up with their primary care providers, but the CL will not be permitted to make any medication/management recommendations.

### Training and quality control

The principal investigator (PI) and the research scientist will conduct study personnel-training sessions on the study protocol and standard operating procedures at the co-ordination center before the initiation of the study including Good Clinical Practice, Human Subject Protection, and Responsible Conduct of Research. The host institute will provide all necessary support for the investigators and in establishing a co-ordination center including seating and training facilities and logistics. The PI will supervise the project implementation by holding biweekly meetings with all the field staff and monthly meetings with all the investigators. The PI will be responsible for upholding the sanctity of the protocol. A Trial Oversight Committee, including subject experts, trial experts, and lay persons, will review the trial’s progress every quarter and provide suggestions for required course corrections. Research fellows will be responsible for identifying potential recruits and obtaining consent. Data will be managed by the research scientist, project co-ordinator, and statistician and saved securely under password-protected access. All clinical data endpoints like interval morbidity will be adjudicated by the Endpoints Adjudication Committee comprising of two diabetologists and a cardiologist independent of the research group and blinded to the intervention/site allocation.

### Duration of treatment and follow-up

After the completion of the intervention, the subjects will be retested for the same parameters (including blood tests) every 3 months till the trial endpoint (18 months for cluster group 1). In the follow-up period, ad hoc query resolution and monthly support group/revision rounds will be conducted by the CL in the cluster till the end of the trial. Each participant will be called by telephone for each session to encourage attendance. All participants will undergo quarterly blood sampling, preventive examination compliance, and drug compliance monitoring every quarter by the research team in coordination with the CL. All participants will be provided with a symptom diary to document the medical issues faced by them through the study period and the direct and indirect costs incurred on diabetes care through the study period. All the participants will be recommended to continue the routine diabetes care, including medicines and doctor visits with their existing care provider and/or preventive checks, and will be assessed for quality of life using the pre-validated QOLID tool at baseline and last follow-up [17]. Cost of care data for both groups will be documented using the cost logs to allow for cost-effectiveness calculations. Any noted new morbidity will be referred to the primary care provider, and the intervention advice will be modified in accordance with the medical advice, even if unblinding is required. Data collection from all participants will proceed as planned irrespective of compliance or shift in residence (by virtual means if required). If consent is withdrawn during follow-up, existing data available with the team till the date of withdrawal will be used as available.

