### Quantitative data

Change in HbA1c before and after the intervention will be evaluated, accounting for SW-CRT design using the swCRTdesign package for R version 4.0.2 and the swSummary function [18]. The sustainability of the effects will be evaluated using the change in quarterly parameters after the intervention is completed. Differences between socio-economic strata will be compared as sub-group analyses depending on the income category of the clusters. Missing data will not be imputed.

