In view of the mounting quantum of evidence, peer-led approaches have gained popularity across the world. However, much of the evidence relates to isolated group-based sessions or peer-led approaches delivered through healthcare facilities or primarily digital interventions. None of the studies reviewed has combined group-based DSME delivered through a community leader with an analogous/complementary digital intervention. Also, there has been limited work from India towards improving the quality of diabetes care using a peer-led approach or digital interventions. The Kerala Diabetes Prevention Program did employ a low-cost-peer-led group education approach in favor of costlier ways. The study documented an improvement in cardiovascular risk factors and HRQOL [33]. Similarly, a trial by Kumar et al. [34] on 300 participants from a hospital in Mysuru found a LSM and medication reminder app to be effective in HbA1c reduction.

A positive result will set the template for a generalizable public health intervention with proven community effectiveness, sustainability, cost-effectiveness, and positive quality-of-life impact. While a negative result will require the testing of alternative approaches, it would still add substantially to existing knowledge on the subject. Given the diverse socio-cultural setting in which the trial is being proposed and the high power of the study, the results (positive or negative) should be widely applicable and have policy implications. The investigators will seek to pursue dissemination of the findings and if positive the refinement and expansion of the intervention to a wider variety of settings.

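### Sustainability is to be judged after the intervention is completed, but community-leader rounds run to trial end, so the data show maintenance under continued support, not persistence after it stops

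*Protocol article*

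**What the plan says.** Under Community leader (CL), the delivered course is a set of 2-hour group sessions held "fortnightly for 3 months". Under Duration of treatment and follow-up, the period after that course has two continuing elements besides the answering of queries as they arise: "monthly support group/revision rounds will be conducted by the CL in the cluster till the end of the trial", and "Each participant will be called by telephone for each session to encourage attendance".

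Under Quantitative data, the analysis is: "The sustainability of the effects will be evaluated using the change in quarterly parameters after the intervention is completed". The abstract's methods paragraph says the same. The sentence before it under Quantitative data has the before-after HbA1c comparison account for the stepped-wedge design. The sustainability sentence does not repeat this and names no model. Secondary outcomes lists sustainability of the gains as a comparison in the groups.

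The text with Fig. 3 gives the schedule: "3 months of data in pre-intervention and 18 months in post-intervention conditions for cluster group 1", then "6 months in pre-intervention and 15 months in post-intervention conditions in cluster group 2, and so on". Phase 3 has every cluster group cross over. The Discussion, in the abstract and in the main text, says that a positive result will set the template for "a generalizable public health intervention with proven community effectiveness, sustainability, cost-effectiveness, and positive quality-of-life impact".

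**The concern.** The period labelled as after completion is not free of the programme. The same community leader, in the same cluster, goes over the material monthly. A flat HbA1c curve in those quarters is what one would see if the benefit outlasts the course. It is also what one would see if the benefit needs monthly support and would fade without it. The design cannot separate the two, because no group at any time has had the course and then no contact.

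The second issue is the comparison. Control clusters run out as the wedge fills, so later quarters lean increasingly on how calendar time is handled. If sustainability is computed as a plain change in quarterly values, any drift in HbA1c over the same months becomes part of the answer.

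What is at stake is a secondary outcome and the policy reading. A planner could conclude that three months of sessions suffice, when the data would support only three months of sessions followed by open-ended monthly rounds.

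**Working it through.** **Schedule.** Group 1 has 3 months before and 18 after crossover; group 2 has 6 and 15. Continuing in 3-month steps, crossovers fall at months 3, 6, 9, 12 and 15, and the trial ends at month 3 + 18 = 21. Group 5 then has 21 − 15 = 6 months after crossover, which matches the 6 to 18 months given under Secondary outcomes. Fig. 3 is not shown, so this rests on the text.

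**Contact after the course.** Follow-up beyond the 3-month course is 21 − crossover month − 3:

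| Group | Crossover (month) | Follow-up after course (months) | Quarterly visits after course (month) |
|---|---|---|---|
| 1 | 3 | 15 | 9, 12, 15, 18, 21 |
| 2 | 6 | 12 | 12, 15, 18, 21 |
| 3 | 9 | 9 | 15, 18, 21 |
| 4 | 12 | 6 | 18, 21 |
| 5 | 15 | 3 | 21 |

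This gives 5 + 4 + 3 + 2 + 1 = 15 cluster-group quarters. The rounds continue to trial end in every cluster, so quarters without community-leader contact number 0 of 15.

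**Concurrent control.** At 6 clusters per group, the untreated clusters at each calendar visit are:

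| Month | 9 | 12 | 15 | 18 | 21 |
|---|---|---|---|---|---|
| A group's visit at its crossover month counts as control | 18 | 12 | 6 | 0 | 0 |
| That visit does not count as control | 12 | 6 | 0 | 0 | 0 |

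- First reading: quarters with a control are group 1 at months 9, 12 and 15, group 2 at 12 and 15, and group 3 at 15. That is 6, leaving 9 of 15 without.
- Second reading: group 1 at 9 and 12, and group 2 at 12. That is 3, leaving 12 of 15 without.
- Per calendar visit, 2 of 5 (or 3 of 5) have no control.

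**What an unadjusted change would contain.** Write δ(e) for the effect at e months since crossover and β(m) for the calendar effect at month m. For group 1, the change from the end of the course (month 6) to trial end (month 21) is

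[δ(18) − δ(3)] + [β(21) − β(6)].

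The second bracket is five quarters of secular change. It drops out only if calendar effects are modelled.

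**The plan's own power figure.** Inputs from Sample size considerations are SD 4.3, ICC 0.09, 12 subjects per cluster, 6 clusters per sequence, 5 steps and a 1% difference. The between-cluster variance is 0.09 × 4.3² = 1.664. The within-cluster variance of a mean of 12 is 0.91 × 4.3² / 12 = 1.402. The Hussey–Hughes model with 6 periods and a constant effect gives SE 0.303. Power is Φ(1/0.303 − 1.96) = 0.91, so the stated 0.90 reproduces (two-sided alpha assumed).

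**The same inputs with a separate effect for each time since crossover.** This uses 8 quarterly visits (months 0 to 21), counts the crossover-month visit as control, and treats measurements as cross-sectional, as in the reproduction above:

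| Months since crossover | 3 | 6 | 9 | 12 | 15 | 18 |
|---|---|---|---|---|---|---|
| SE of effect | 0.316 | 0.378 | 0.454 | 0.547 | 0.662 | 0.836 |
| Power for 1% | 0.89 | 0.75 | 0.60 | 0.45 | 0.33 | 0.22 |
| SE of change from 3 months | – | 0.325 | 0.376 | 0.451 | 0.560 | 0.745 |

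The design matrix has full rank, so every effect is estimable. The 95% half-width for the change from 3 months is 1.96 × 0.325 = 0.64 points at 6 months and 1.96 × 0.745 = 1.46 points at 18 months. If half of the within-cluster variance is a stable person effect (an assumption; the article gives no figure), power for 1% runs from 0.99 at 3 months to 0.37 at 18. The SE of the change at 18 months is then 0.541, a half-width of 1.96 × 0.541 = 1.06 points.

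**The case against.** The article is open about the monthly rounds and separates the course from the follow-up period. Its stated aim concerns the sustainability of a community-leader-based rollout, so sustainability can fairly be read as gains holding under the local model once the intensive course ends. That reading is reasonable, but the article nowhere adopts it, and the analysis sentence points to a completed intervention. Adopting the reading explicitly is the remedy.

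The Discussion sentence is conditional and forward-looking, not a result. It still says what a positive trial would be taken to prove.

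Four stronger readings are tempting, and the documents do not support them:

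- **That the plan prescribes a raw calendar-time change.** The text never says raw or unadjusted. It is brief, and model terms may sit in an analysis plan that is not shown. What can be said is that the sustainability sentence is not tied to the stepped-wedge analysis as the HbA1c sentence is, and that an unadjusted change would be confounded.
- **That most later quarters lack a control.** This holds for cluster-group quarters (9 or 12 of 15). On the first reading it fails for calendar visits (2 of 5).
- **That effects at months 18 and 21 cannot be estimated and must be purely descriptive.** With common period and exposure-time effects, group 5 (then 3 and 6 months past crossover) anchors the calendar effects, because effects at those exposure times are estimated from earlier groups. The cost is dependence on the model and lower precision.
- **That running out of controls is a design error.** It is inherent in a stepped wedge. The point is only that the analysis and wording must allow for it.

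**Conclusion.** The concern holds in this limited form. The analysis wording and the follow-up section have to be reconciled: all 15 cluster-group quarters after the course measure maintenance under continued monthly support, and none measures persistence after support stops. Nine of the 15 (12 if group 5's month-15 visit is not control) have no concurrent untreated cluster, so period adjustment is essential. The latest effects depend on a common-period-effect assumption and are imprecise: power for 1% falls from 0.89 at 3 months since crossover to 0.22 at 18.

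The counts rest on the schedule reconstructed from the text. The precision figures rest on the article's SD and ICC, and on cross-sectional measurements except where a person effect is stated. The concern affects a secondary outcome and the sustainability conclusion only, and should be corrected before results are read.

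**What to change.** 1. In the abstract's methods, Duration of treatment and follow-up, Quantitative data and Secondary outcomes, define the outcome in one way: maintenance of effect under continued monthly community-leader support after the 3-month course. This changes the label, not the programme.
2. In both Discussion passages, limit the sustainability conclusion to that definition.
3. Estimate it as effects by time since crossover in a mixed model with calendar-quarter effects and random effects for cluster and participant. Report the change from the 3-month effect with its interval.
4. State that estimates at months 18 and 21 have no concurrent control, rest on the common-period-effect assumption and are less precise. State also whether a group's visit in its crossover month counts as control.

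The cost is wording and additional model terms, with no new data. The price is a narrower claim and wider intervals for late effects. The primary comparison at 3 months is unchanged.
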